## Abstract

**Background:**

Today, while there are effective drugs that reduce the risk of osteoporotic fracture, yet there are no broadly accepted criteria that can be used to estimate risks and decide who should receive treatment. One of the actual priorities of clinical research is to develop a set of simple and readily-available clinical data that can be used in routine clinical practice to identify patients at high risk of bone fracture, and to establish thresholds for therapeutic interventions. Such a tool would have high impact on healthcare policies. The main objective of the ESOSVAL-R is to develop a risk prediction scale of osteoporotic fracture in adult population using data from the Region of Valencia, Spain.

**Methods/Design:**

*Study design*: An observational, longitudinal, prospective cohort study, undertaken in the Region of Valencia, with an initial follow-up period of five years; *Subjects*: 14,500 men and women over the age of 50, residing in the Region and receiving healthcare from centers where the ABUCASIS electronic clinical records system is implanted; *Sources of data*: The ABUCASIS electronic clinical record system, complemented with hospital morbidity registers, hospital Accidents & Emergency records and the Regional Ministry of Health's mortality register; *Measurement of results*: Incident osteoporotic fracture (in the hip and/or major osteoporotic fracture) during the study's follow-up period. Independent variables include clinical data and complementary examinations; *Analysis*: 1) Descriptive analysis of the cohorts' baseline data; 2) Upon completion of the follow-up period, analysis of the strength of association between the risk factors and the incidence of osteoporotic fracture using Cox's proportional hazards model; 3) Development and validation of a model to predict risk of osteoporotic fracture; the validated model will serve to develop a simplified scale that can be used during routine clinical visits.

**Discussion:**

The ESOSVAL-R study will establish a prediction scale for osteoporotic fracture in Spanish adult population. This scale not only will constitute a useful prognostic tool, but also it will allow identifying intervention thresholds to support treatment decision-making in the Valencia setting, based mainly on the information registered in the electronic clinical records.

## Background

Osteoporosis is a systemic disease of the skeleton, characterized by the deterioration of the bones' macro and microstructures that leads to a loss in bone mass and the reduction in the bones' resistance increasing propensity to bone fracture [1]. At present, osteoporosis is highly prevalent, with an incidence that is rising due to the greater life expectancy of today's societies. Osteoporosis is a silent disease, yet has a major clinical impact because of its association with an increased risk of fracture. The most relevant events associated with osteoporosis are osteoporotic fractures and their consequences. Most frequently, events occur in the dorsolumbar spine, the hip and the wrist.

Hip fracture is the most serious consequence of osteoporosis. In Spain it is estimated an incidence of hip fracture in people over 50 years-old between 2-3 cases per 1,000 inhabitants/year [2-5], with a male/female distribution of 2-3:5. These figures increase considerably with age, and in subjects over the age of 60, the incidence of hip fracture is 5-7 cases per 1,000 inhabitants/year, with greater occurrence among women [6,7]. Regarding vertebral fractures, prevalence and incidence rates vary considerably, depending on the population and the criteria used to define a fracture. In subjects over the age of 50 in the Region of Asturias, Spain, prevalence was 27.2% in women and 20.8% in men [8]. In a population-based study recently conducted by our group in post-menopausal women in the city of Valencia, the prevalence of morphometric vertebral fracture was 21% in women over 50, and 46% in women over 75 [9].

According to data recently published in the Region of Valencia, Spain [10] the annual number of hospital admissions for fractures of the hip, vertebrae and forearm (fractures that are not due to major traumatism assessed using the Hospital Discharge Data Set) has increased in absolute values in the population over the age of 64. Discharges in the Region for hip fracture have gone from 3,329 in 2000 to 4,510 in 2006. Distal fractures of the forearm went from 341 to 496 during the same period. The number of vertebral fractures -that usually are managed without hospitalization- remained stable. Osteoporotic fracture has major social and health impact. Mortality for hip fracture in hospitalized patients is between 5 and 8%, and jumps to 20-30% during the first year [11]; only one third of survivors recover their pre-fracture condition.

Today, while there are effective drugs that reduce the risk of osteoporotic fracture, yet there is no broadly accepted criteria that can be used to estimate risks and decide who should receive treatment. One of the actual priorities of clinical research is to develop a set of simple and readily-available clinical data that can be used in routine clinical practice to identify patients at high risk of bone fracture, and to establish thresholds for therapeutic interventions. Such a tool would have high impact on healthcare policies. Because hip fracture is associated with the greatest disease burden, efforts are being concentrated in this area.

Studies have shown that the loss of bone mineral density (BMD), as measured by dual energy x-ray absorptiometry (DXA) is a good predictor of fracture, particularly in older women. The risk of osteoporotic fracture nearly doubles for each standard deviation decrease in BMD [12,13]. Nevertheless, there are many other factors that contribute to osteoporotic fracture, and the loss of BMD only identifies part of the risk. Studies have shown that normal BMD does not mean that there is no risk of osteoporotic fracture. Some of the Clinical Risk Factors (CRFs) involved in osteoporotic fracture only affect bone mass, and may be used to identify thresholds for testing with BMD. Other CRFs are associated with increased risk of osteoporotic fracture independently of BMD [14,15], and looking at these will improve the prediction of risk fracture [16,17]. For these reasons, different proposals have been forwarded to estimate the risk of osteoporotic fracture taking into account the different CRFs (as occurs when estimating the risk of cardiovascular events), with or without information on BMD.

This tools aims to predict the risk of an incident osteoporotic fracture during a specific period of time, usually ten years. Black et al [18], with their Fracture Index, were among the first to propose a set of criteria to predict vertebral, non-vertebral and hip fractures. More recently, Robins et al. [19], and Vazquez et al., in Spain [20], have proposed other scores although today FRAX is the scale most widely accepted internationally [21].

Robins et al. [19] developed a risk prediction scale for hip fracture at five years in post-menopausal women using data from the Women's Health Initiative study. The CRFs used in this scale include age, general health, weight, height, race, physical activity, personal history of fragility fracture after the age of 45, parental history of hip fracture, smoking habits, current use of corticoids and diabetes under treatment. Vazquez et al. [20] looked at a cohort in Rotterdam to evaluate the risk of hip and vertebral fracture at ten years in function of the subject's age and a risk score. The CRFs these authors examine are BMD (<19), history of fracture before the age of 50, parental history of hip fracture and the presence vertebral deformities. The usefulness of this index in our context has not yet been established, since it does not include treatment criteria, and still needs to be validated in the Spanish population.

The FRAX scale has been backed by the World Health Organization and its use has been rapidly widespread. It examines CRFs either independently or in combination with BMD to evaluate the risk of osteoporotic fracture at ten years, in men and women over the age of 50. The FRAX can be used to predict the probability of hip or other major osteoporotic fracture (clinical spine, hip, forearm or humerus). Predictors include age, sex, weight, height, history of prior fragility fracture, parental hip fracture, current smoking, long-term use of oral glucocorticoids, diagnosis of rheumatoid arthritis, secondary osteoporosis and alcohol consumption. The BMD of the hip is included as a non-clinical factor. The original study did not define criteria for treatment, but two later papers have used cost-utility analysis techniques to recommend treatment thresholds for the United Kingdom [22] and the United States [23]. These criteria, as the authors themselves point out, cannot be generalized to other countries with different fracture incidence rates and different healthcare costs.

The most recent score for estimating the individual risk of osteoporotic fracture or hip fracture over 10 years has been developed by Hippisley-Cox et al [24] in the UK population. These new risk prediction algorithms (QFractureScores) for osteoporotic fracture and hip fracture do not require laboratory measurement and so can be used in primary care or for individual self assessment. The validation statistics, especially for the hip fracture algorithm, suggest that the QFractureScores are likely to be useful for identifying patients at high risk of fracture in the primary care setting in the UK and showed improved performance compared with FRAX.

The main implication of these results is that when developing a scale for a specific population, or recalibrating an international scale to the fracture incidence of a given country, local data must be collected. Local studies will focus on a highly heterogeneous population that represents the real risks of a given region, and will help to establish osteoporosis treatment thresholds.

The Valencia Health Agency, the public healthcare network that covers close to 93% of the inhabitants of the Region of Valencia, has implanted an electronic medical record system called ABUCASIS. This population-based electronic database allows carrying out longitudinal studies of all the patients attending the healthcare centers from the Region of Valencia, enabling the monitoring of most relevant clinical data. It is now possible to do a low-cost cohort study that will ultimately lead to developing a risk scale with a 5-10 year window for patient follow-up.

The main objective of the ESOSVAL-R is to develop a risk prediction scale of osteoporotic fracture using data from the Region of Valencia. This scale will allow identifying intervention thresholds to support treatment decision-making in the Valencia setting, based mainly on the information registered in the electronic clinical records.

## Methods/Design

### Main objective

To develop and validate a risk prediction scale for osteoporotic fracture in the adult population of the Region of Valencia, Spain.

### Specific objectives

1. To describe baseline characteristics of the cohort under study and the prevalence of risk factors for osteoporosis. This objective will reveal the current prevalence of risk factors for osteoporosis in men and women over 50 years in the Region of Valencia.

2. To evaluate the strength of association between risk factors and the incidence of osteoporotic fracture at five years for the overall population over the age of 50, and for the five-year age-sex subgroups. This objective will also be developed specifically for the risk of hip fracture.

3. To analyze using survival models the time relationship between risk factors and the incidence of osteoporotic fracture and the risk of hip fracture.

4. To identify in patients with osteoporotic and hip fracture factors of poor prognostic for survival.

5. To develop and validate a prediction scale for the risk of osteoporotic fracture at five years, specific to the population of the Region of Valencia, Spain.

6. To evaluate the calibration and the discrimination capacity of the FRAX scale in the population of the Region of Valencia and, if necessary, to recalibrate this scale for its use in the Valencia population.

### Design

This is an observational, longitudinal, prospective cohort study with a minimum follow-up period of five years (that can be prolonged to a maximum of ten years, depending on the incidence of the most infrequent event, hip fracture). The data used in the study will be obtained primarily from the electronic clinical records (ABUCASIS system). Complementary sources of information will also be used to identify the follow-up outcomes.

### Setting

The sample will be recruited from the Region of Valencia (Spain) and, specifically, the population receiving healthcare from the Valencia Health Agency.

### Population and sample

Women and men 50 years of age and over, residing in the Region of Valencia receiving health care in centers where the ABUCASIS electronic clinical record system has been implanted. Exclusion criteria included: 1) Non-residents in the Region of Valencia, due to limitations for long-term follow-up; 2) Individuals with cognitive impairments that in the opinion of the collaborating clinicians constitutes a hindrance to collecting information about the variables used in the study; 3) People eligible for public healthcare but receiving services through private insurance companies, due to the limitations for collecting data; 4) People who are physically unable to attend their usual primary healthcare center; institutionalization is not a criterion for exclusion as long as the patient can go to the healthcare center; 5) People of Asian or African decent, because of differences in prevalence of osteoporosis due to ethnic origin. The cohort will be recruited opportunistically from among the patients who attend the collaborating primary care centers during a 15-week period.

The sample size has been calculated with the stpower Cox utility of the STATA^® ^statistics package, under the following assumptions: Alpha error (0.05), power (0.80), standard deviation for the densitometry T-score (0.75), square of the multiple correlation among co-variables (0.10), losses to follow-up of 10%, accumulated incidence of hip fracture of 15‰ after five years of follow-up and a capacity to identify as significant hazard ratios of 33% (change in the frequency of an event associated with a unit of change in the co-variable). These calculations results in a sample size of 14,122 individuals over the age of 50 in whom 180 hip fractures are expected to occur at five years of follow-up. The sample will be distributed according to the age and sex structure of the population over the age of 50 in the Region of Valencia and will be assigned in groups of 36 cases among the approximately 400 participating "practices" (two collaborating health care professionals, typically with one doctor and one nurse, per "practice") in order to be able to build a sample that is faithful to the structure of the population of the Region.

### Data sources

The main source of data will be the ABUCASIS electronic clinical records. For the outcome variables, this source will be completed with hospital morbidity records (Discharge Data sets and other systems being implanted), hospital accident and emergency records, and the regional Ministry of Health's mortality registry. Baseline data, including the patient's risk factors at the time of recruitment into the cohort, will be collected during the initial visit, using a new modified version of the ABUCASIS specifically developed to collect information about the variables used in the study that were not routinely found in clinical records. The results of previous exams (x-rays or densitometry) that may have been performed on the patients will be included in the initial evaluation (information about previous fractures and densitometry values). In the case of densitometry results, the information that will be included in the initial evaluation will be from examinations done in a period of ± 2 years at the time of recruitment.

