### Main endpoint

This study's main endpoint is a major osteoporotic fracture that occurs during the follow-up period of the study. Major osteoporotic fracture is defined as a new fracture of the hip (not present at the time of recruitment), a clinical fracture of the vertebrae or a proximal fracture of the humerus or wrist. Fractures derived from severe traumatism (traffic accidents, collisions, gravitational trauma) will not be included, nor will pathological fractures due to other causes (bone cancer, metastasis to the bone, and Paget's disease established through diagnosis).

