### Other variables

The independent variables used in this study were selected after reviewing the literature and current practice guidelines, and includes the patient's age, gender, weight and height with a calculation of the BMI, smoking habits, drinking habits, exercise habits, history of parental hip fracture, low calcium intake, untreated hypogonadism in men or women, rheumatoid arthritis, other metabolic bone diseases excluding hypogonadism, use of oral glucocorticoids, use of drugs affecting bone metabolism other than glucocorticoids, previous osteoporotic fracture, high risk of fall, prolonged immobilization, densitometric osteoporosis of the lumbar spine established through DXA (T score for L2-L4), densitometric osteoporosis of the hip established through DXA in the total hip or the femur neck (T score) and treatments for osteoporosis. The participating physicians will be trained in the management of these variables and will be given a procedures manual containing all pertinent definitions. Information about antiresorptive treatment will be collected from the GAIA system, the electronic prescription system associated with the ABUCASIS that currently covers 95% of all prescriptions dispensed in the Region. It records all the information about the drug prescribed, along with its dosage and the length of treatment.

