### Ethical aspects

The study will be conducted according to the international standards of the International Guidelines for Ethical Review of Epidemiological Studies (Council for International Organizations of Medical Sciences-CIOMS-Geneva, 1991) and the recommendations of the Spanish Society of Epidemiology about the review of ethical aspects of epidemiological research.

The ESOSVAL-R study has been reviewed and approved by the Committee for Ethics and Clinical Trials of the Center for Public Health Research. The ESOSVAL-R is a naturalistic, observational study undertaken as part of routine clinical practice, with no intervention (apart from training of participating clinicians) with the patients included in the study. No additional risks associated with participation are anticipated, as no additional diagnosis, evaluation or treatment will be provided, apart from what the attending physician deems appropriate.

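### The ± 2-year densitometry window contradicts its own paragraph and, read literally, lets T-scores measured after recruitment count as baseline

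*Protocol article*

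**What the plan says.** All of the following is in the protocol article.

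- **Data sources, timing of baseline:** "Baseline data, including the patient's risk factors at the time of recruitment into the cohort, will be collected during the initial visit".
- **Data sources, earlier examinations:** "The results of previous exams (x-rays or densitometry) that may have been performed on the patients will be included in the initial evaluation".
- **Data sources, next sentence:** the densitometry information "will be from examinations done in a period of ± 2 years at the time of recruitment".
- **Outcome counting, in the section headed Main endpoint, which defines the event as follows:** "This study's main endpoint is a major osteoporotic fracture that occurs during the follow-up period of the study". A hip fracture counts as new if it was not present at recruitment, so outcome counting starts at recruitment.
- **Other variables:** the candidate predictors include the lumbar-spine T-score and "densitometric osteoporosis of the hip established through DXA in the total hip or the femur neck (T score) and treatments for osteoporosis".
- **Ethical aspects:** "no additional diagnosis, evaluation or treatment will be provided, apart from what the attending physician deems appropriate". Scanning is therefore left to routine care.
- **Design and Statistical analysis:** the cohort is followed "with a minimum follow-up period of five years", and associations are analysed at two and at five years. The scale is built on a random two-thirds of the sample and checked on the remaining third.

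No section limits the scans to those before recruitment, or to those before a fracture. The misclassification item in the Discussion concerns old versus new fractures, not the date of a scan.

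**The concern.** A baseline predictor has to be known at time zero. A scan done 18 months after recruitment is neither a previous examination nor something available at the initial visit, yet the ± window accepts it. Three consequences follow.

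1. **Availability can depend on the outcome.** Scans are ordered at the physician's discretion, and a new fracture is a plausible reason to order one. Patients with early fractures could then be over-represented among those with a T-score.
2. **Later scans carry event-free time.** A patient scanned after recruitment without having fractured has, by construction, stayed fracture-free until the scan.
3. **The tool would not be used that way.** When risk is estimated in practice, only past scans exist.

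The planned validation offers no protection. A random third of the same database is extracted under the same window, so the C statistic and the Hosmer-Lemeshow test would be computed on data with the same defect. At the two-year analysis the plus side of the window covers the whole of follow-up. The FRAX evaluation is exposed as well wherever hip bone density is used in it.

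**Working it through.** **The plan's own figure.** The only number tied to the T-score is the sample size (Population and sample). Inputs: two-sided alpha 0.05 (sidedness is not stated; two-sided reproduces the result), power 0.80, T-score SD 0.75, squared multiple correlation 0.10, hazard ratio 1.33 per unit, 5-year hip-fracture incidence 15 per 1,000, losses 10%.

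- Events = (1.960 + 0.842)² / [0.75² × (ln 1.33)² × (1 − 0.10)] = 190.6
- N = 190.6 / 0.015 / 0.90 = 14,121, against 14,122 stated

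The stated N reproduces. It shows that the sample size was built around the T-score. The timing point does not depend on it.

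**How much of follow-up the window overlaps.** Assume a constant hazard that gives 15 per 1,000 at five years: λ = −ln(1 − 0.015)/5. The share of five-year hip fractures falling in the first two years is (1 − e^(−2λ))/0.015 = 0.402, or about 72 of the 180 the article expects. At the two-year analysis the share is 100%.

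**Effect on absolute risk among patients with a T-score.** The documents give no scanning rates, so every input here is assumed: fracture risk r5 = 5% at five years and r2 = 2% at two years; a proportion *pre* scanned before recruitment regardless of outcome; among the rest, 5% of those fracture-free at two years scanned in the plus window, and a proportion *f* of those who fracture in that time scanned afterwards.

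- Scanned = pre + (1 − pre)·r2·f + (1 − pre)·(1 − r2)·0.05
- Events among scanned = pre·r5 + (1 − pre)·r2·f + (1 − pre)·(r5 − r2)·0.05

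| pre | f | Scanned | Events | Apparent 5-year risk | Ratio to 5.0% | Events scanned after fracture |
|---|---|---|---|---|---|---|
| 10% | 5% | 0.1450 | 0.00725 | 5.0% | 1.0 | 12% |
| 10% | 20% | 0.1477 | 0.00995 | 6.7% | 1.35 | 36% |
| 10% | 40% | 0.1513 | 0.01355 | 9.0% | 1.8 | 53% |
| 20% | 20% | 0.2424 | 0.01440 | 5.9% | 1.2 | 22% |
| 20% | 40% | 0.2456 | 0.01760 | 7.2% | 1.4 | 36% |

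The first row is the null: equal scan rates with and without fracture give no inflation. The event-free-time effect works the other way. In this simplified model, with pre = 10% and f = 0, scanned = 0.1441 and events = 0.00635, an apparent risk of 4.4%.

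**A second illustration, for hip fracture.** Suppose a proportion *q* of 10–30% have a scan regardless of outcome, and a proportion *s* of 10–40% of cases without one are scanned after a fracture in years 0–2. The proportion of cases with a T-score is p = q + (1 − q)·s·0.402. The share of those T-scores that post-date the fracture is (p − q)/p, which runs from 9% (q = 30%, s = 10%) to 59% (q = 10%, s = 40%). The odds ratio for having a T-score, case against non-case, runs from 1.14 to 2.92 with no true relation. At s = 0 it is 1.

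**What the arithmetic does not cover.** Neither model contains T-score values. They address who has a T-score and the absolute risk in that group, not the hazard ratio per unit of T-score or the C statistic.

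**The case against.** The strongest reply is that the surrounding text points to scans on or before recruitment. The neighbouring sentences speak of earlier examinations and the initial visit, and the Follow-up section again places collection of the risk variables at that visit. The ± sign may be loose wording for about two years. The procedures manual mentioned under Other variables, which is not shown, may settle the definition.

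This stands to the extent that the article shows a contradiction, not a settled plan to use scans taken after a fracture. A reader might infer that plan from the ± sign, but the documents do not support it. Nor do they say that fractures trigger scans; that is an inference from scanning being left to the physician. The reply does not cure the text, however. The window is a stated rule, nothing in the article overrides it, and an extract programmed from it would take in later scans.

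The second objection is to the size. The inflated rows assume scanning 4 to 8 times as common after fracture (20–40% against 5%), and equal rates give none. The model also gives a fracture at month 23 the same chance of a scan within the window as one at month 1. And it describes patients with a T-score, for whom the article plans no separate analysis; the handling of missing T-scores may properly sit in a document not shown. These points stand, so the figures are illustrations only.

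Third, the T-score is one of many candidates and the final model is to be parsimonious, so it may not enter the scale. That limits the reach of the problem but does not justify the window.

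**Conclusion.** The point holds as a contradiction within Data sources, with a foreseeable consequence. Read literally, the window overlaps the period in which outcomes are counted, for a predictor whose measurement is left to clinical discretion. The likely effect is distorted absolute risk, and hence calibration, among patients with a T-score. Under the assumed rates the apparent 5-year risk lies between no inflation and about 1.8 times the true value. The real size is unknown, and it is small if few later scans occur.

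A reader might go further and conclude that the T-score hazard ratio is biased by reverse causation, or that the scale will look more accurate than it is. Both are possible, but neither is shown. If a fracture changes only whether a scan exists, and not its value, the relative association and the discrimination need not be materially affected. Reverse causation proper would need the T-score itself to change after the fracture, and the documents give nothing on that.

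**What to change.** Reword the sentence in Data sources so that densitometry comes from *examinations done in the 2 years up to and including the recruitment visit*, in line with the sentences around it. Keep the scan date in the extract, apply a date filter, and use no scan dated after recruitment as a baseline predictor in the scale. If later scans are of interest, use them only from their own date, as a time-updated covariate outside the risk scale.

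Excluding only the scans taken after a fracture would not be enough. It would leave the event-free-time effect, which is the 4.4% case in the working.

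The cost is one sentence, one filter, and somewhat fewer patients with a T-score.
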